## Abstract

**Background:**

Surgical site infections are the third most frequent type of nosocomial infections. Evidence-based recommendations have been given regarding preoperative hospitalization, hygiene and air-conditioning, patient conditions, and wound dressing. However, no general recommendations concerning wound closure exist. Systematic reviews and meta-analyses suppose a benefit of intracutaneous suture compared to skin staples in orthopedic and obstetric surgery. Literature data for skin closure in elective abdominal surgery are still deficient.

**Methods/Design:**

Patients scheduled for any elective abdominal surgery requiring midline or horizontal laparotomy are potentially eligible for the trial. Trial-specific exclusion criteria are date of admission exceeding four days prior to surgery, antibiotic treatment within the past 14 days, any previous midline or horizontal laparotomy in case the procedure requires the same skin incision as before, neurophysiological deficits or severe psychiatric or neurologic diseases that do not allow an informed consent or compliance, and participation in any other interventional trial with interference of intervention and outcome. The trial is created for process innovation within standardized surgical procedures. It is designed as a prospective randomized controlled single center trial in a parallel design including an active comparator and an intervention group. The intervention addresses the closure of skin after the main surgical procedure: intracutaneous suture in the intervention group and transcutaneous skin stapling in the control group. The rate of superficial surgical site infections is defined as the primary endpoint. Secondary endpoints are time for skin closure, satisfaction with the cosmetic outcome 30 days after surgery, prolongation of hospital stay, and duration of sick-leave due to surgical site infections. The primary efficacy analysis follows the intention-to-treat principle. A χ^2^ test will be applied.

**Discussion:**

The trial is expected to balance the shortcomings of the current evidence. It will help to define the gold standard for wound closure in elective abdominal surgery. Patients’ safety and quality of life are assumed to be enhanced. Therapy costs are likely to be reduced and health care optimized.

**Trial registration:**

German Clinical Trials Register (DRKS)
DRKS00004542.

## Background

The prevention of surgical site infections is one of the basic issues in the study of any surgical discipline to enhance quality of health care and patient safety. Over the past decades, this attempt led to the constitution of national institutes for disease surveillance and prevention. For diagnostic purposes, an internationally acknowledged classification for surgical site infections has been outlined by the Center of Disease Control (CDC), Atlanta, USA, within a guideline for prevention in 1999. According to their location and source, surgical site infections are categorized by severity and implications. In Germany, CDC-criteria were adopted by the National Institution for Disease Surveillance and Prevention (Robert Koch Institute) and implemented within the National Reference Center for Surveillance of Nosocomial Infections
[1]. A national representative prevalence study (NIDEP-1-trial) demonstrated surgical site infections to be the third most frequent type of nosocomial infections with an incidence of 16%
[2], affecting 128,000 patients per year
[3] and with a prolonged hospital stay ranging between 9.5 to 23.7 days
[4]. Besides patient safety and quality of life, postoperative surgical site infections are of economic relevance, since hospital treatment costs increase by 2.8-fold on average
[3]. For example, in the USA, the total economic load due to nosocomial infections was calculated to have reached 95 million USD in 1992
[3].

The main source for surgical site infections is the patients’ own flora, which despite evidence-based preoperative antisepsis, still causes endogenous infections with a proportion of 90% compared to 10% of exogenous infections due to contamination by any external agent
[5]. In systematic reviews, meta-analyses, and randomized controlled trials, the length of hospitalization, antisepsis of patient’s skin, surgeons’ hands, operation site, depilation, air-conditioning of the operation room, patient’s temperature, and wound drainage and dressing have proven to be influential in wound healing. Subsequently, standards and recommendations have been outlined by national surveillance institutions
[6]. However, no general recommendation for the technique of skin closure exists to date. Staples and different types of sutures are used in clinical routine. Alternatively, adhesive stripes and tissue adhesive DERMABOND ProPen® and Op-site® films are especially favored to close small incisions
[7,8]. Results of randomized controlled trials assessing the impact of different closure techniques on superficial surgical site infections are conflicting in dependence of body region and surgical procedure. Differences in the bacterial spectrum and number of bacteria are likely to be influential. In orthopedic surgery, a meta-analysis comparing the outcome of sutures versus staples on superficial surgical site infections demonstrated superiority of sutures for knee and hip surgery. However, the authors outlined substantial methodological limitations of the primary data and the need for definite randomized controlled trials
[9]. In heart surgery, a systematic review of randomized controlled trials for closure of leg wounds after vein graft harvesting for coronary artery bypass surgery revealed no difference between sutures and staples
[10]. In obstetrics, a recent systematic review and meta-analysis demonstrated the superiority of subcuticular sutures compared to staples for skin closure after caesarean sections; there was no significant difference in the cosmetic outcome
[11].

Regarding abdominal surgery, five randomized controlled trials dating from 1981 to 1992, assessed the outcome of staples versus sutures for skin closure on superficial surgical site infection, pain, operation time, and cosmetic outcome. Three of the trials compared interrupted mattress sutures to staples
[12-14], and two compared intracutaneous sutures versus staples
[15,16], including a comparison of different suture materials
[16]. While in the Pickford trial
[14] the infection rate was significantly lower in favor of staples (6.3% vs. 17%), no significant difference could be demonstrated in the trials of Eldrup
[12] and Gatt
[13]. The two trials comparing intracutaneous sutures to staples showed no significant difference regarding the incidence of superficial surgical site infection. Moreover, the suture material was proven to be of no impact
[16]. All trials, which additionally considered the cosmetic outcome
[13,15,16] and closure time, revealed no significant difference for the cosmetic outcome but a significant reduction of the closure time. However, data addressing postoperative pain were conflicting. Two trials demonstrated a significant reduction of postoperative pain in favor of staples
[12,15], whilst one trial showed no difference
[13]. Although the evidence is usually classified as “Ib” according to the trial design, the methodology is deficient referring to power calculation, calculation of the effect sizes, allocation, and methods for minimizing bias and blinding, as well as calculation of outcomes when using multiple endpoints. The limitations are explicable considering the methodological progress and consolidated standards of conducting and reporting trials within the past two decades. A recent interdisciplinary meta-analysis of randomized controlled trials investigating the impact of staples versus sutures for skin closure of abdominal wounds shares the same limitations
[17]. Altogether, infection rates did not differ significantly comparing suture and staples for skin closure and there were no significant differences in the cosmetic outcome; the primary data were derived from obstetrics and gynecology, general surgery, head and neck surgery, vascular surgery, and emergency care
[17]. Despite heterogeneity having been found as not significant, the primary data bear substantial methodological limitations.

Most of the trials above had multiple primary endpoints; neither a calculation of the effect size nor power was reported, and suture materials and techniques varied. To outbalance conflicting results and a lack of evidence, prospective randomized controlled trials are needed to define the ideal closure technique for skin incisions in abdominal surgery.

## Methods/Design

A retrospective analysis of in-house data has been done to prepare the calculation of the sample size and power. This trial manuscript was prepared thereafter. The local ethics committee of the Philipps-University of Marburg gave a positive approval on October 2, 2012 (leading ethics committee number 190/12). The trial is registered at the German Clinical Trials Register (DRKS) (trial number DRKS00004542). Financing is granted through an in-house funding program of the Philipps-University Marburg and Rhoen-AG. The preparation of electronic case report forms, database, and data management system is established.

### Eligibility

Patients scheduled for any elective abdominal surgery requiring a midline or horizontal laparotomy are potentially eligible for the present study. Surgical procedures comprise small bowel and large bowel resection, rectal surgery including laparoscopic assisted colorectal resections with Pfannenstiel incision exceeding six centimeters in length, esophageal, gastric, duodenal, and pancreatic surgery, liver resections, open cholecystectomies with or without choledochotomies, gastro-intestinal and intestinal-intestinal bypass anastomosis, bilio-digestive anastomosis, and splenectomies. After a screening visit, patients will be allocated to the trial according to the below mentioned inclusion and exclusion criteria. Additionally, patient specific risk factors such as age, gender, American Society of Anesthesiologists (ASA)-status, body mass index, diabetes, steroid intake, and smoking habits will be recorded. Before enrolment, an informed consent will be obtained from each patient.

### Inclusion criteria

Key inclusion criteria are scheduled for any elective abdominal surgery using midline or horizontal laparotomy, age greater than or equal to 18 years, expectancy of life greater than 12 months, and informed consent.

### Exclusion criteria

Exclusion criteria are date of admission exceeding four days prior to surgery, antibiotic treatment within the past 14 days, any previous midline or horizontal laparotomy if the procedure requires the same skin incision as before, neurophysiological deficits or severe psychiatric or neurologic diseases that do not allow an informed consent or compliance, participation in any other interventional trial with interference of intervention and outcome, and inability to understand patients’ information and informed consent form.

### Intervention and control

The study is designed as a prospective, randomized, controlled, single center clinical trial in a parallel design including an intervention group and an active comparator. The intervention addresses the type of skin closure in an elective abdominal surgery. In the intervention group, skin closure is performed by intracutaneous suture using Monosyn® 4-0. Skin staples are used in the control group. After the closure of the fascia, patients are randomly assigned to an intervention or control group by intraoperative randomization. Thereafter, the length of the incision and the thickness of the subcutaneous tissue at its thickest point is measured and recorded. The subcutaneous wound is prepared for closure according to the local in-house standard: lavage with diluted chloramine (0.05%), suction drain and closure by absorbable inverting interrupted single stitches. The standard is maintained to control potential confounders of superficial surgical site infections. When the intervention is applied, the time to close the skin is measured and recorded. Further, intraoperative complications such as relevant contaminations of the abdominal cavity which require an additional lavage, extensive blood loss exceeding 500 ml, intraoperative cardiovascular complications or resuscitations, and the total operation time (from the skin incision to skin closure) are registered.

Either the responsible surgeon, or the first or second assistant may close the skin. No special surgical expertise is required since skin stapling and intracutaneous suture are basic surgical skills acquired at the very beginning of surgical training or even in medical training. Altogether, 27 surgeons, including the head of the department, consultants, senior and junior registrars, will participate in the study.

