### Surgical methods

Both types of skin closure–transcutaneous stapling and intracutaneous suture–are considered safe and standardized techniques in abdominal surgery. The main surgical procedures are not influenced by the trial protocol. After surgery and closure of the abdominal wall and subcutaneous tissue, merely the type of skin closure will be determined through randomization. The trial is designed for process innovation within standardized therapeutic surgical procedures in an elective setting. No new surgical technique is applied.

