#### Secondary endpoints

Secondary endpoints comprise time of skin closure, satisfaction of the cosmetic outcome 30 days after surgery, prolongation of hospital stay, and inability to work due to surgical site infections. After randomization and closure of the subcutaneous tissue, the time of skin closure is recorded. Within the follow-up visits, the satisfaction of the cosmetic outcome 30 days after surgery is assessed separately by the patient and an independent wound manager on a scale as used within the German school grade system (1?=?best to 6?=?worst). Moreover, the prolongation of hospital stay and employees’ illness due to surgical site infections are recorded.

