### Randomization, allocation concealment, and blinding

A random sequence will be generated through computerized random assignment and concealed allocation. Intraoperative randomization will be performed. After closure of the fascia, the anesthetist or the second scrub nurse calls the randomization office to give the patient’s number, surgeon’s name, and ask for allocation. Using the loudspeaker, the surgeon then is de-blinded. The outcome assessment cannot be blinded due to the nature of the study. Therefore, the detection bias is high and cannot be minimized. Skin staples will be visible for the outcome assessors during the follow-up visits from days 1 to 10.

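### The protocol gives two orders for randomization and subcutaneous closure; in the order most sections use, the arm is known while the endpoint's own tissue layer is treated, so performance bias can enter

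*Protocol article*

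**What the plan says.** Three sections of the protocol article put randomization before the subcutaneous work.

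- **Intervention and control:** "After the closure of the fascia, patients are randomly assigned to an intervention or control group by intraoperative randomization". The next sentence reads "Thereafter, the length of the incision and the thickness of the subcutaneous tissue at its thickest point is measured and recorded". The subcutaneous wound is then prepared by the in-house standard: "lavage with diluted chloramine (0.05%), suction drain and closure by absorbable inverting interrupted single stitches". The stated purpose is: "The standard is maintained to control potential confounders of superficial surgical site infections".
- **Randomization, allocation concealment, and blinding:** "After closure of the fascia, the anesthetist or the second scrub nurse calls the randomization office", followed by "Using the loudspeaker, the surgeon then is de-blinded".
- **Secondary endpoints:** "After randomization and closure of the subcutaneous tissue, the time of skin closure is recorded". Randomization is named before subcutaneous closure here too.

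One section gives a different order.

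- **Surgical methods:** "After surgery and closure of the abdominal wall and subcutaneous tissue, merely the type of skin closure will be determined through randomization".

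Two further sections bear on the consequences. Under Primary endpoint, the infection that counts is one confined to skin and subcutaneous tissue. Under Statistical analysis, the primary comparison is an unadjusted two-sided chi-square test, and subcutaneous fat thickness appears only among the covariates of the logistic regression used as a sensitivity analysis.

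**The concern.** The trial is meant to isolate the effect of the skin closure technique. That requires everything done to the wound before skin closure to be independent of the arm. If the arm is announced once the fascia is closed, the team knows it while handling the subcutaneous layer. That layer is part of the tissue in which the primary endpoint is defined, and the protocol itself treats these steps as relevant to superficial infection. A difference between arms in the care with which they are done would then be counted as an effect of suture or staples, in either direction.

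This is not the limitation that the protocol already concedes. The concession is about detection bias, because outcome assessors can see staples at follow-up. The point here is performance bias before skin closure. Unlike the conceded bias it is avoidable, since nothing in the document requires the arm to be known before the subcutaneous layer is closed.

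**Working it through.** **1. The order of steps, side by side**

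| Section | Randomization relative to subcutaneous closure |
|---|---|
| Intervention and control | Before: after the fascia, then measurement, then subcutaneous steps |
| Randomization, allocation concealment, and blinding | Before: call after the fascia, surgeon told immediately |
| Secondary endpoints | Before, by the order in which the two are named |
| Surgical methods | After, read literally |

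The last row cannot be followed together with the first two.

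**2. What falls between disclosure and skin closure in the first order**

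- Recording of incision length and subcutaneous thickness.
- Lavage, drain and subcutaneous stitches. These concern tissue inside the primary endpoint definition.

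**3. The plan's own figure**

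Inputs from Sample size: 14% and 4%, two-sided 5%, power 80%, 10% drop-out. With mean rate 0.09:

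n = [1.960·√(2·0.09·0.91) + 0.842·√(0.14·0.86 + 0.04·0.96)]² / 0.10² = 127.4, so 128 per group.

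Total: 256 / 0.9 = 284.4, so 285. The stated figures reproduce, and the timing of the call does not alter them.

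**4. What a difference in subcutaneous care could do (illustration only)**

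Assume that skin closure has no effect, 128 patients per group are analysed, and a difference in subcutaneous handling alone separates the infection rates. The size of that difference is assumed; the document gives none. The rejection probability is the sum of Bin(x; 128, p₁)·Bin(y; 128, p₂) over all pairs (x, y) for which the uncorrected chi-square test is significant at 5%.

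| Assumed rates | Shift (points) | Rejection probability |
|---|---|---|
| 14% vs 14% | 0 | 4.9% |
| 14% vs 13% | 1 | 5.5% |
| 14% vs 12% | 2 | 7.4% |
| 14% vs 11% | 3 | 11.0% |
| 14% vs 10% | 4 | 16.3% |
| 9% vs 9% | 0 | 5.0% |
| 9% vs 10% | 1 | 5.9% |
| 9% vs 12% | 3 | 12.2% |
| 9% vs 14% | 5 | 23.8% |

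The 14% is the protocol's staple rate, and 9% is the mean of its two planning rates. A normal approximation agrees closely (14% vs 12%: 7.6%; 14% vs 10%: 16.6%).

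A 1-point shift barely matters. A shift of 3 points or more at least doubles the nominal error rate. For scale, the whole planned effect is 14 − 4 = 10 points, so a 5-point shift would be half of it.

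**5. The covariate**

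Thickness is anatomical and is measured before the subcutaneous and skin layers are closed, so neither technique can change it. Only measurement error related to knowledge of the arm remains. The primary chi-square test does not use it.

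**The case against.** **The subcutaneous steps are standardized.** The protocol applies one in-house standard to both arms precisely to control confounding. This stands as mitigation. It names the steps, but it cannot fix how thoroughly each is carried out by an operating team that knows the arm, with 27 participating surgeons from junior registrar to head of department. So the risk is reduced, not removed.

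**The conflict may be loose wording.** The Surgical methods sentence can be read as saying what randomization determines rather than when it happens, and three sections agree on the other order. This is a fair reading. It makes fascial closure the likely working sequence, which is the order that leaves the subcutaneous steps exposed. The wording needs reconciling on either reading.

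**The illustrated shifts may be too large.** This also stands. The larger ones are considerable for care that the protocol standardizes, and with a 1-point shift the error rate is nearly nominal.

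**Stronger readings that the document does not support.** A reader might infer any of the following:

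- That bias has in fact entered the result. The document shows exposure only.
- That thickness is measured by the unblinded surgeon. The text does not say who measures.
- That the person closing the skin is chosen once the arm is known. The text lets the surgeon or either assistant close, and does not say when this is decided.
- That the late thickness measurement biases the primary result. It cannot, because the primary test is unadjusted.

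**Conclusion.** The concern holds as a contradiction that must be reconciled and as an avoidable opening for performance bias. The contradiction is plain from the text. That bias can enter under the order in Intervention and control and in the randomization section follows from two stated facts: the arm is disclosed before the subcutaneous steps, and the primary endpoint covers that tissue.

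The size is unknown. The rejection rates above, from about 5.5% with a 1-point shift to 23.8% with a 5-point shift, rest on assumed differences and on no true effect of skin closure. They show sensitivity and do not estimate what has happened. The consequence of recording thickness after disclosure is confined to the adjusted sensitivity analysis. The sample size is not in question.

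**What to change.** Amend Intervention and control, Secondary endpoints, and the randomization section to one sequence:

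1. Fascia closed.
2. Incision length and subcutaneous thickness recorded.
3. Subcutaneous layer closed by the existing standard.
4. Call to the randomization office.
5. Arm announced immediately before skin closure.

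This agrees with the Surgical methods section and makes thickness a pre-randomization covariate.

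The cost is small but not nil. Ethics approval dates from 2 October 2012 and enrolment began on 4 March 2013, so if the team has been calling after fascial closure this is a procedural amendment during recruitment. The sponsor should document which order was used for patients already randomized, and from what date the new order applies. The treatments, the number of patients, the test and the endpoint are unchanged.

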### Statistical analysis

The primary hypothesis is that the rate of superficial surgical site infections within 30 days after elective abdominal surgery via midline or horizontal incision is lower in patients after intracutaneous closure of the skin when compared to closure of the skin by staples. The primary efficacy endpoint will be assessed as a rate, defined as the number of patients who experienced a superficial surgical site infection (type A1) within 30 days after surgery divided by the number of all patients randomized to this arm. Infections of types A2 or A3 are not defined as primary events. For the intention-to-treat analysis, these patients will be considered within the denominator. The primary analysis will be done in the intent-to-treat population. To compare the incidence rates in both arms, a two-sided χ^2^ test will be applied. As sensitivity analyses, a χ^2^ test for the per-protocol population will be applied as well as logistic regression analyses adjusting for potential prognostic factors: diagnosis and procedure, age, gender, ASA-status, body mass index, diabetes, steroid intake, smoking, and thickness of subcutaneous fat. The secondary efficacy endpoints will be analyzed exploratively. Appropriate summary measures for the empirical distributions as well as two-sided 95% confidence intervals and *P* values will be reported. The safety analysis will be applied to the safety population comprising all patients operated.

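### Nothing requires the person who closes the skin to be chosen before the allocation is announced, so operator experience could differ between the arms

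*Protocol article*

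**What the plan says.** Under Intervention and control, the Protocol article gives the timing: "After the closure of the fascia, patients are randomly assigned to an intervention or control group by intraoperative randomization". Measurement of the incision, preparation of the subcutaneous layer and skin closure all follow.

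The section Randomization, allocation concealment, and blinding says how the allocation reaches the team. The anesthetist or second scrub nurse "calls the randomization office to give the patient’s number, surgeon’s name, and ask for allocation". Then: "Using the loudspeaker, the surgeon then is de-blinded".

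On who performs the allocated method, Intervention and control says: "Either the responsible surgeon, or the first or second assistant may close the skin". Its reason is that "No special surgical expertise is required since skin stapling and intracutaneous suture are basic surgical skills". The pool is wide: "Altogether, 27 surgeons, including the head of the department, consultants, senior and junior registrars, will participate in the study".

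Two other statements set the aim. Surgical methods says that randomization determines nothing except the type of skin closure. Intervention and control says that the wound-preparation standard is kept so that confounders of superficial infection are controlled.

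In Statistical analysis, the primary test is an unadjusted two-sided chi-square test. The adjusted sensitivity analysis lists "diagnosis and procedure, age, gender, ASA-status, body mass index, diabetes, steroid intake, smoking, and thickness of subcutaneous fat". Among the secondary endpoints: "Secondary endpoints comprise time of skin closure, satisfaction of the cosmetic outcome 30 days after surgery". These are analysed exploratively.

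**The concern.** Randomization balances what is settled before the allocation is known. The operating team is settled by then. Which of its members will close the skin need not be, because the article permits three people and sets no moment by which one of them must be chosen. A team that has just heard the method could give the quicker one to one grade and the slower one to another, without breaking any stated rule.

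If that happened, the arms would differ in who closed as well as in how. The trial attributes its result to closure type, and the two could not be separated. The chi-square test has no operator term, and the listed covariates describe the patient, the diagnosis and the procedure. Adding the actual closer to the model later would mean adjusting for something that the allocation may itself have influenced.

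Closure time is the most exposed endpoint, since it partly measures the operator's speed. Cosmetic satisfaction and A1 infection could also be affected, less directly.

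**Working it through.** **1. Order of events.** The sections Intervention and control and Randomization, read together, give this sequence: fascia closed; call made with patient number and surgeon's name; allocation announced by loudspeaker; incision measured and subcutaneous layer closed; skin closed by one of three people. The call as described has two items, and neither is tied to the person who will close. An interval remains after the announcement in which the closer can still be chosen.

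**2. The plan's own figure.** Inputs from Sample size: 14% with staples, 4% with suture, two-sided 5%, power 80%. The mean rate is 9%.

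n per group = [1.96 × √(2 × 0.09 × 0.91) + 0.8416 × √(0.14 × 0.86 + 0.04 × 0.96)]² / 0.10² = (0.7933 + 0.3354)² / 0.01 = 127.4, so 128. Power at 128 is 80.2%. Total: 256 / 0.90 = 284.4, so 285. The stated sample size reproduces, and this point does not change it.

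**3. Illustration for A1 infection.** The documents give no infection rates by operator and no shares of closures by grade, so every operator input here is assumed:
- there is no true method effect;
- the average risk is 9% when juniors close half the wounds;
- the junior-to-senior risk ratio (RR) is 1.3 to 2.0 and is the same in both arms;
- the share closed by juniors differs between arms by 20 to 60 percentage points.

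Senior risk = 9% / (0.5 + 0.5 × RR); junior risk = RR × senior risk. Shift = difference in junior share × (junior risk − senior risk).

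| RR | Senior / junior risk | 20 points | 40 points | 60 points |
|---|---|---|---|---|
| 1.3 | 7.83% / 10.17% | 0.47 | 0.94 | 1.41 |
| 1.5 | 7.20% / 10.80% | 0.72 | 1.44 | 2.16 |
| 2.0 | 6.00% / 12.00% | 1.20 | 2.40 | 3.60 |

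The middle cell, 1.44 points, is about one seventh of the 10-point target difference. The standard error at 9% and 128 per arm is √(2 × 0.09 × 0.91 / 128) = 3.58 points, so the shift is 1.44 / 3.58 = 0.40 standard errors. The two-sided rejection rate with no method effect is then about Φ(−1.96 + 0.40) + Φ(−1.96 − 0.40) = 0.060 + 0.009, or roughly 7% in place of 5%. At RR 1.5 with junior shares of 30% and 50% it is 5.5%; at 20% and 80% it is 9.3%.

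**4. If experience matters for suture only.** The difference in share between arms is then the wrong multiplier. What counts is how far the junior share in the suture arm moves from what it would have been had the closer been fixed beforehand. Take 4% at a half-and-half mix and RR 1.5: senior 4% / 1.25 = 3.2%, junior 4.8%. Moving the junior share by 20 points shifts the suture rate by 0.20 × 1.6 = 0.32 points; by 40 points, 0.64. For scale, a suture rate one full point higher (5% against 14%) would reduce power at 128 per group from 80% to 69%.

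**5. Direction.** The shift favours whichever arm is closed more often by the lower-risk grade. The documents do not say which arm that would be, so the shift could imitate a benefit of suture or hide one.

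**6. Closure time.** The documents give no times, so no figure is offered. The link needs no infection model: an operator's speed enters the measurement directly.

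**The case against.** The case against is substantial, and much of it stands.

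- **Nothing shows that teams choose by arm.** The article never says that the closer is picked after, or because of, the allocation. A reader might infer that it does; the text only fails to prevent it. When the closer is chosen could be operational detail in a fuller document. What keeps the point alive is that the article itself sets the rule on who may close, gives a reason for it and lists the contents of the call.
- **The surgeon named in the call might be the person who closes.** The wording is open to that reading. But two of the three permitted closers are assistants, and the article does not link the name given to the act of closing.
- **The choice is narrow.** A reader might take the 27 surgeons as the field of choice. They are not: each closure falls to one of at most three people already operating, and the make-up of that team precedes allocation and is balanced by randomization.
- **This is not classical confounding.** Delegation prompted by the allocation lies downstream of randomization. The intention-to-treat comparison remains valid for a policy of assigning a method, including how teams then staff it. The article, however, frames the question as closure type alone and keeps other steps standard, so the narrower reading fits its stated aim better.
- **Both methods are called basic skills.** That is an assertion about competence. It may well mean that the effect on infection is small, but it does not make operators equally fast.
- **The most exposed endpoint is exploratory.** This is true, and it limits the consequence.

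**Conclusion.** The point holds as a gap in procedure. The stated rules allow the choice of closer, among at most three people, to depend on an allocation already announced, and the planned analyses could not undo the result. Closure time is most directly exposed and carries no confirmatory claim.

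For A1 infection an effect is possible, with unknown size and direction. The 1.4-point figure and the range of 0.5 to 3.6 points rest wholly on an assumed risk ratio, an assumed imbalance in junior share and an equal operator effect in both arms. They are smaller if experience matters only for suture. They show scale and do not estimate bias.

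A reader might go further and conclude that the primary comparison is confounded or its type I error badly inflated. The documents do not support that. Under the same no-effect model, a false-positive rate as high as 32.6% requires junior shares of 20% and 80% and a risk ratio of 3, and nothing in the article points to such values. This is a cheap improvement, not a flaw that undermines the primary endpoint.

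**What to change.** In Intervention and control and in Randomization, allocation concealment, and blinding, add that the team names the person who will close the skin, with grade, during the existing call and before the allocation is given. That person then closes by whichever method is allocated. Any switch is recorded with its reason, and the patient stays in the allocated arm for the intention-to-treat analysis.

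The named closer's grade would then be fixed before allocation. It could be added to the sensitivity logistic regression as a baseline factor, without adjusting for something the allocation had influenced.

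The cost is a sentence in the protocol, one more item in the call and one eCRF field. The small downside is less flexibility when the named person is called away, which recording the switch covers. Who may close the skin, the sample size and clinical management are unchanged. Enrolment began on 4 March 2013, so the rule would apply to patients still to be randomized.
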